# The efficacy and safety of acupuncture combined with language training for motor aphasia after stroke: study protocol for a multicenter randomized sham-controlled trial

**DOI:** 10.1186/s13063-022-06280-2

**Published:** 2022-06-30

**Keywords:** Motor aphasia, Acupuncture, Sham acupoints, Language training, RCT, WAB, CFCP, Study protocol

## Abstract

**Background:**

Motor aphasia after stroke is a common and intractable complication of stroke. Acupuncture and language training may be an alternative and effective approach. However, the efficacy of acupuncture and language training for motor aphasia after stroke has not been confirmed. The main objectives of this trial are to evaluate the effectiveness and safety of acupuncture and low-intensity, low-dose language training in treating ischemic motor aphasia after stroke from 15 to 90 days.

**Methods:**

This is a multicenter randomized sham-controlled clinical trial. We will allocate 252 subjects aged between 45 and 75 years diagnosed with motor aphasia after stroke with an onset time ranging from 15 to 90 days into two groups randomly in a 1:1 ratio. Patients in the experimental group will be treated with “Xing-Nao Kai-Qiao” acupuncture therapy plus language training, and those in the control group will be treated with sham-acupoint (1 cun next to the acupoints) acupuncture therapy plus language training. All the patients will be given acupuncture and language training for 6 weeks, with a follow-up evaluation 6 weeks after the end of the treatment and 6 months after the onset time. The patients will mainly be evaluated using the Western Aphasia Battery and Chinese Functional Communication Profile, and the incidence of treatment-related adverse events at the 2nd, 4th, and 6th weeks of treatment will be recorded. The baseline characteristics of the patients will be summarized by group, the chi-squared test will be used to compare categorical variables, and repeated measures of analysis of variance or a linear mixed model will be applied to analyze the changes measured at different time points.

**Discussion:**

The present study is designed to investigate the effectiveness and safety of traditional acupuncture therapy and language training in ischemic motor aphasia after stroke and explore the correlation between the treatment time and clinical effect of acupuncture. We hope our results will help doctors understand and utilize acupuncture combined with language training.

**Trial registration:**

ChiCTR ChiCTR1900026740. Registered on 20 October 2019

**Supplementary Information:**

The online version contains supplementary material available at 10.1186/s13063-022-06280-2.

## Administrative information

Note: The numbers in curly brackets in this protocol refer to SPIRIT checklist item numbers. The order of the items has been modified to group similar items (see http://www.equator-network.org/reporting-guidelines/spirit-2013-statement-defining-standard-protocol-items-for-clinical-trials/).

**Table Taba:** 

Title {1}	The efficacy and safety of acupuncture combined with language training for Motor Aphasia after stroke: study protocol for a multicenter randomized sham-controlled trial
Trial registration {2a and 2b}.	Chinese Clinical Trial Registry: ChiCTR1900026740 Registry Name: A randomized controlled trial for “Xing-Nao Kai-Qiao” Rehabilitation Program in the Treatment of Motor Aphasia after Stroke Item 2b: An additional movie file shows this in more detail [see Table 1]
Protocol version {3}	Date: 20 October 2019 Version identifier: V1.1
Funding {4}	This study was funded by the National Key Research and Development Program of China [No. 2018YFC1706001].

Name and contact information for the trial sponsor {5b}	Special funds from the central government of China
Role of sponsor {5c}	The sponsor provides funding to support the design of the study, execution, analysis, interpretation of the data, and decision to submit the results.

**Table 1 Tab1:** Trial registration data

Data category	Information
Registration number	ChiCTR1900026740
Date of last refreshed on	October 22, 2019
Date of registration	October 20, 2019
Registration status	Prospective registration
Public title	A randomized controlled trial for “Xing-Nao Kai-Qiao” Rehabilitation Program in the Treatment of Motor Aphasia after Stroke
Scientific title	A randomized controlled trial for “Xing-Nao Kai-Qiao” Rehabilitation Program in the Treatment of Motor Aphasia after Stroke
The registration number of the Partner Registry	AMCTR-IOR-19000302
Study leader	[name]
Study leader’s address	[name]
Approved no. of the ethics committee	TYLL2019[K]word015
Primary sponsor	The First Affiliated Hospital of Tianjin University of Traditional Chinese Medicine
Source(s) of funding	Central government special funds
Target disease	Aphasia after stroke
Study type	Interventional study
Study design	Parallel
Inclusion criteria	(1) Meet the diagnostic criteria for motor aphasia after stroke; (2) aphasia appears for the first time after stroke; (3) onset time ranged from 15 days to 3 months; (4) the severity of aphasia is 0–3, which can be used in conjunction with speech training; (5) consciousness of consciousness and stable vital signs; (6) aged 45 to 75 years old; (7) patient or family signed an informed consent form and have a good compliance
Exclusion criteria	(1) Combined with severe primary diseases such as liver, kidney, hematopoietic system, and endocrine system; (2) there are abnormalities in audio-visual, severe cognitive impairment, and mental illness, which cannot be combined with examination and treatment; (3) pregnant and lactating women
Recruiting time	From October 21, 2019, to December 31, 2020
Countries of recruitment	China
Primary outcomes	Western Aphasia Battery; Functional Language Communication Capability Check
Secondary outcomes	Boston Diagnostic Aphasia Examination; NIH Stroke Scale; SAQOL-39 Quality of Life Scale; Stroke-Specific Quality of Life Scale; the Health Scale of Traditional Chinese Medicine
Randomization procedure	Stratified block randomization method
Blinding	Open label
The time of sharing IPD	Within 6 months after the trial complete
The way of sharing IPD	Apply to the main researcher for publication

## Introduction

### Background and rationale {6a}

#### Justification for undertaking the trial

Motor aphasia after stroke (MAAS) is one of the critical complications associated with ischemic stroke because it leads to harmful effects in patients and a significant economic burden to society [1]. Aphasia was reported in approximately 21 to 38% of acute ischemic stroke patients [1–3].

As a Traditional Chinese Medicine (TCM) therapy, acupuncture has been utilized in China for thousands of years. It is effective in treating MAAS to improve functional communication and language function [4]. Additionally, acupuncture has demonstrated positive changes in motor speech symptoms or “motor” aphasia [5]. Some studies have revealed that acupuncture has therapeutic advantages in spontaneous speech, repetition, naming, and daily communication for MAAS patients [6, 7]. Acupuncture may be effective in motor aphasia, but methodological weaknesses in many studies compromise firm conclusions about its efficacy. Thus, the effectiveness of acupuncture must be confirmed in rigorously designed studies with solid evidence from more trial data [8–10].

#### Summary of relevant studies

Presently, transcranial direct current stimulation (tDCS), non-invasive brain stimulation (NIBS), novel speech-language therapy (SLT), pharmacological treatments, and some alternative treatments have been reported to treat motor aphasia after stroke [11]. Although some positive effects have been achieved, some limitations have also been reported in clinical applications. For example, pharmacological treatments might improve the recovery from aphasia after stroke. However, no drug has been proven to produce an overall favorable effect [12]. Language training improves oral naming accuracy for trained items in patients with aphasia, with long-term gain maintenance over time [13]. Thus, SLT may be beneficial at high intensity, high dose, or over a longer period; however, it is not suitable for all patients [14]. Additionally, tDCS and NIBS lack sufficient evidence to improve language function [14, 15].

#### Research question

The main objectives of this trial are to evaluate the efficacy and safety of acupuncture and low-intensity, low-dose language training in ischemic motor aphasia after stroke from 15 to 90 days.

### Objectives {7}

Research hypothesis: “Xing-Nao Kai-Qiao” acupuncture combined with language training is an effective approach for MAAS, and its efficacy is superior to sham-acupoint acupuncture and language training.

Study objectives: To assess the efficacy and safety of “Xing-Nao Kai-Qiao” acupuncture combined with language training on ischemic MAAS from 15 to 90 days.

### Trial design {8}

The clinical study is designed as a multicenter randomized sham-controlled clinical trial. A total of 252 participants will be randomized into two parallel groups at a 1:1 ratio, including the acupuncture group and the sham acupuncture group. Each eligible subject will undergo a 6-week treatment period, followed by a follow-up period of 6 weeks after treatment and 6 months after onset time. Six visits in total are scheduled for each subject at weeks 0, 2, 4, and 6; 6 weeks after treatment; and 6 months after onset time (Table 2).

**Table 2 Tab2:** Trial process chart

Period		Screening	Treatment			Follow-up	
Items		Before enrolment (weeks) −2 to −1	End of 2-week treatment (weeks) 3	End of 4-week treatment (weeks) 5	End of 6-week treatment (weeks) 7	End of 6 weeks after the end of the treatment follow-up (weeks) 13	End of 6 months after the onset time follow-up
Recruitment		X					
Enrolment		X					
Inclusion criteria		X					
Exclusion criteria		X					
Basic characteristic variables		X					
Randomization and allocation concealment		X					
Primary outcomes	Western Aphasia Battery	X	X	X	X	X	X
	Chinese Functional Communication Profile	X	X	X	X	X	X
Secondary outcomes	X	X	X	X		X	X
	National Institute of Health Stroke Scale	X	X	X	X	X	X
	Stroke and Aphasia Quality of Life Scale-39	X	X	X	X	X	X
	Stroke Specific Quality of Life Scale	X	X	X	X	X	X
	Health Scale of Traditional Chinese Medicine	X	X	X	X	X	X
Adverse events recorded			X	X	X		
Relapse						X	X
Self-reported drug therapy			X	X	X	X	X
Compliance			X	X	X		

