#### Secondary outcomes

The secondary outcome measures were WAB scale scores and CFCP scale scores, assessing the difference between the two groups at 6 months after onset time; Boston Diagnostic Aphasia Examination (BDAE) [19] scores for the severity of the language competence status; Stroke and Aphasia Quality of Life Scale-39 (SAQOL-39) [20] and Stroke-Specific Quality of Life Scale (SS-QOL) [21] scores for the quality of living in stroke patients; National Institute of Health Stroke Scale (NIHSS) [22] scores for the neurological deficit; Health Scale of Traditional Chinese Medicine (HSTCM) [23] scores for the health status, assessing the difference between the two groups after 6 weeks of treatment and 6 months after onset time. The study’s adverse events and dropout causes will be recorded in a case report form (CRF).

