### Adverse event reporting and harms {22}

Subcutaneous bleeding or hematoma around acupoints during acupuncture therapy and pain around acupoints related to acupuncture are expected adverse reactions and do not need to be reported to the ethics committee. Only unexpected serious adverse events, such as deterioration and death from all causes throughout the treatment period, should be reported immediately to the principal investigator and further to the ethics committee. All details will be recorded, and appropriate medical attention will be given immediately.

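### Adverse events other than relapse that start after week 6 have no scheduled collection, although the safety objective has no time limit and patients attend two later visits

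*Protocol article*

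**What the plan says.** **Objective.** The Research question section sets out to "evaluate the efficacy and safety of acupuncture and low-intensity, low-dose language training", and Objectives {7} states the aim as "To assess the efficacy and safety of “Xing-Nao Kai-Qiao” acupuncture combined with language training on ischemic MAAS from 15 to 90 days". Neither limits safety to a period; the range of days describes time since onset.

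**Visits.** Trial design {8}: "Each eligible subject will undergo a 6-week treatment period, followed by a follow-up period of 6 weeks after treatment and 6 months after onset time". It continues: "Six visits in total are scheduled for each subject at weeks 0, 2, 4, and 6; 6 weeks after treatment; and 6 months after onset". Under section {18b} the two follow-up visits are outpatient re-examinations with a travel subsidy.

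**Safety schedule.** In Table 2, "Adverse events recorded" is marked only in the three treatment columns. Relapse is marked only in the two follow-up columns. Self-reported drug therapy is marked at all five post-baseline visits, and the NIHSS at every visit. The abstract says that "the incidence of treatment-related adverse events at the 2nd, 4th, and 6th weeks of treatment will be recorded".

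**Reporting.** Section {22}: "Only unexpected serious adverse events, such as deterioration and death from all causes throughout the treatment period, should be reported immediately to the principal investigator". Onward reporting goes to the ethics committee.

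**Other mentions.** Under Secondary outcomes, adverse events and dropout causes go into the case report form, with no time window. Section {18b} names scale measurement, medication evaluation and general follow-up information as the tasks at follow-up, without naming adverse events. Section {11b}, on discontinuing or modifying the intervention, refers to adverse events and all-cause death within an observation period that the article does not define.

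**The concern.** Efficacy is compared up to 6 months after onset, but the adverse-event row stops at the end of treatment. Benefit and harm would then be judged over different windows, although the objective draws no such distinction. No analysis plan can repair this afterwards, because an event that was never asked about cannot be analysed.

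Two related points follow. First, relapse is a named row only after treatment. A recurrence in weeks 1 to 6 would be entered as an adverse event, and one after week 6 as a relapse. The same event is held in different places by period, so a comparison from first treatment to last visit needs a rule to join them. Second, the abstract speaks of treatment-related events, while Table 2 and Secondary outcomes speak of adverse events without that limit.

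At stake is a safety statement for the whole trial that rests on the treatment period alone.

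**Working it through.** The article gives no coverage figure, so there is none to reproduce. The check has two parts.

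**1. What is scheduled in each period**

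- *Weeks 1 to 6:* the adverse-event row, the NIHSS, drug therapy and compliance; immediate reporting of unexpected serious events and deaths.
- *After week 6:* relapse, the NIHSS and drug therapy; unspecified follow-up information; documented causes of dropout. There is no adverse-event row, and immediate reporting is not extended to this period.

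A recurrent stroke after week 6 is therefore collected, and neurological worsening would show on the NIHSS. A death would be seen only as a reason for dropout. Any other adverse event starting after week 6 has no scheduled entry. Table 2 also labels the treatment visits weeks 3, 5 and 7 where the text says 2, 4 and 6; this is only a difference in numbering.

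**2. Share of calendar time covered**

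Inputs:
- Recording window: 6 weeks = 42 days (Trial design {8}, Table 2).
- Entry: day 15 to day 90 after onset (Abstract; Eligibility criteria {10}).
- 6 months after onset: 180 to 183 days (assumption; no day count is given).
- Treatment starts on the day of entry (assumption, relaxed below).
- Last visit: the later of 6 months after onset and 84 days after treatment start (6 weeks of treatment plus 6 weeks).

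Formula: coverage = 42 / (day of last visit − day of treatment start).

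| Start day | 6 months = 183 days | 6 months = 180 days |
|---|---|---|
| 15 | 42/(183 − 15) = 42/168 = 25.0% | 42/(180 − 15) = 42/165 = 25.5% |
| 60 | 42/123 = 34.1% | 42/120 = 35.0% |
| 90 | 42/93 = 45.2% | 42/90 = 46.7% |

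For a day-90 start the 12-week visit falls on day 90 + 84 = 174, so the 6-month visit is still the last. If entry at day 90 is followed by a 14-day gap (the longest interval in the screening column of Table 2), treatment starts on day 104. The 12-week visit, on day 188, is then the last, and coverage is 42/84 = 50%. Only such a gap brings the figure to a half.

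The days without an adverse-event row run from 90 − 42 = 48 (start on day 90, 180-day convention) to 168 − 42 = 126 (start on day 15, 183-day convention).

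Against needling exposure, coverage is 42/42 = 100%.

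**The case against.** The strongest reply is that calendar time is the wrong denominator. Recording spans the whole course of needling. The reactions the protocol expects (bleeding or haematoma under the skin and pain at the needling site) arise during treatment, and no delayed harm of acupuncture is named. An on-treatment safety window is a legitimate design. This stands: a reader might infer that half to three quarters of harms go unrecorded, and the documents do not support that.

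A reader might also infer that nothing after week 6 can enter the safety comparison. That is too strong. Relapse and the NIHSS are collected at both follow-up visits. Section {30} has adverse events managed until they resolve, so an event that began in treatment is already on record. The case report form entry has no stated time limit, and dropout causes are to be documented in detail.

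A third inference is that a recurrence during treatment is missed. It would fall in the adverse-event row. What remains is the split of one event type across two rows.

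A fourth is that only events judged related, by staff who know the arm, are counted. The limit to related events appears only in the abstract, and the article does not say who judges relatedness. What remains is a wording mismatch.

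Finally, this is a condensed article, and the case report form and investigator manual are not shown. They may ask for more. But Table 2 is an explicit schedule, the abstract agrees with it, and section {18b} names no adverse-event task at follow-up. The gap is in what is stated, not in what was left out.

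**Conclusion.** The point holds in a limited form. As scheduled, adverse events other than relapse that start after week 6 are not systematically collected, and late deaths would surface only as reasons for dropout. This is so although safety is an objective without a time limit and patients attend two later visits in person. The window covers all of the needling period and about 25% to 47% of calendar time from treatment start to last visit. That range assumes that 6 months is 180 to 183 days and that treatment starts at entry. It describes time observed, not the fraction of harms missed, which the documents do not allow anyone to estimate.

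The treatment period in section {22} and the observation period in section {11b} also need reconciling. One governs immediate reporting and the other discontinuation, so neither settles the collection window. The efficacy analysis is unaffected. The change is worth making because it is cheap and cannot be made after the data are in.

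**What to change.** - In Table 2, mark the adverse-event row at both follow-up visits, at least for serious events and deaths.
- Record all adverse events, with relatedness as a separate field, and word the abstract to agree with Secondary outcomes.
- Define relapse and count it in both periods, so that arms can be compared from first treatment to last visit.
- Reconcile the period terms in sections {11b} and {22}, and define each.

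If adverse events are not added at follow-up, state in the objectives that the safety comparison covers the 6-week treatment period only. The same statement is needed in the results if follow-up has already closed; the Trial status section planned to end recruitment on 31 December 2020.

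The cost is a few extra case report form fields and a little more data entry at visits that already take place.

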## Methods: participants, interventions, and outcomes

### Study setting {9}

The patient data will be collected throughout the clinical trial in China at three level-III hospitals in Tianjin, Changchun, and Jinan.

### Eligibility criteria {10}

Inclusion criteria:
Subjects diagnosed with ischemic stroke according to the International Classification of Diseases code ICD-10-I63.902 [16]Subjects diagnosed with aphasia for the first time after strokeSubjects diagnosed with aphasia ranged from 15 to 90 daysSeverity of aphasia of 0–3 can be combined with speech trainingAwake consciousness and stable vital signsSubjects aged between 45 and 75 years, male or femaleSubjects and their families fully understand the research content and agree to participate in the study and sign the informed consent form

Exclusion criteria:
Subjects diagnosed with aphasia not caused by strokeSubjects with aphasia before the onset timeSubjects with severe heart disease and kidney and liver function insufficiencySubjects with audio-visual abnormalities, severe cognitive impairment, and mental illness cannot cooperate with examination and treatmentPregnant or lactating women

Dropout criteria:
Subjects have poor compliance during the clinical study and are unwilling to accept the intervention and withdraw voluntarilySubjects experience severe adverse reactions or deterioration during the clinical study and are not eligible for further intervention

### Who will take informed consent? {26a}

Before the start of clinical studies, trained researchers will introduce the trial to patients and discuss the trial with patients considering the information informed, including the research nature, research purpose, possible benefits and dangers, meeting the requirements of the Declaration of Helsinki, and the rights and obligations of the subjects. Patients will be able to have informed discussions with researchers. The subjects or their legal representative will understand, agree, and sign the written informed consent. Researchers will obtain written consent from patients willing to participate in the trial.

### Additional consent provisions for collection and use of participant data and biological specimens {26b}

Not applicable. We have not designed ancillary studies.

## Interventions

### Explanation for the choice of comparators {6b}

Acupuncture therapy and language training are recommended as a control group. Manipulators should choose acupoints that are 1 cun away from the acupoints of the verum acupuncture group. The stimulating amount of acupuncture requires no “De Qi” sensation. Sham-acupoint acupuncture mainly consists of some sham acupoints not located on the meridians and have no therapeutic effect on aphasia.

### Intervention description {11a}

Subjects in the experimental group will receive verum acupuncture and language training, and those in the control group will receive sham-acupoint acupuncture and language training. Additionally, common drugs used in the neurological department are allowed, such as anti-hypertensive drugs and antiplatelet drugs, which are included in the Guidelines for the Diagnosis and Treatment of Integrated Traditional Chinese and Western Medicine in Cerebral Infarction in China (2017). The same individuals will deliver the trial interventions in all the study groups.

